### **Study Duration and Phases:**

The overall study duration is 24 months. It consists of three major phases (Fig. 1).

#### **Phase 1: Preparation Phase (8 months):**

**Design questionnaires:** In this phase, project questionnaires will be finalized.

1. Diabetes Treatment Satisfaction Questionnaires (DTSQ): The questionnaire will be used to assess diabetes-related treatment satisfaction (pre and post-intervention). The questionnaire was designed by [name], University of London, UK, and has been previously validated in Saudi Arabia.
2. 24-hour dietary recall: This will be used to assess energy and nutrient intakes. This tool was used in a national nutrition survey conducted in the UAE in 2009/2010.
3. Diabetes knowledge: This questionnaire covers nutrition knowledge related to food sources of carbohydrates, fiber, fat, saturated fat, and cholesterol. This questionnaire was developed by the research team from the related literature (Ali et al, 2008; Talbot et al 1997). The questionnaire will be tested for face and content reliability and modified accordingly before the intervention starts.
4. Physical activity questionnaire: The International Physical Activity Questionnaire (IPAQ) – Short Form (Booth, 2000)

**Research ethics approval:** During the Preparation Phase ethical approval for the project will be obtained from the relevant research ethics committees (UAE University Research Affairs Research Ethics Committee and Al Ain Medical District Human Research Ethics Committee)

**Staff training:** All project staff will attend training to ensure that research procedures will be followed. Dietitians, nurse educators, and physicians who will be involved in the patient education will attend a 3-day training and orientation program. Topics that will be discussed include: An update on nutritional management of diabetes, adult education principles, and application of the relevant behavioral change theories in nutrition counseling (including motivational interviewing, stages of change model, and social cognitive theory), and physical activity counseling. The training will be conducted in the format of a workshop and will use skill-building teaching methods, such as case studies and role plays.

**Phase 2: Intervention Phase (12 months):**

After obtaining verbal and informed consent and immediately after recruitment, all research participants will undergo detailed nutrition and other baseline assessments (dietary, anthropometric, biochemical, diabetes treatment satisfaction, and physical activity levels). In this phase, a 12-month diabetes nutrition education intervention will be implemented in three Ambulatory Healthcare Services clinics in Al Ain. The impact of the educational intervention will be evaluated at the end of the 12-month intervention by comparing data obtained from intervention and “usual care” (control) health centers.

**Phase 3: Post-Implementation Phase (4 months):** This phase involves data entry, data analyses, and preparation of the project's final report.

[figure not shown]

Fig. 1. Project Phases & Activities

### Data collection:

The data collection plan at baseline and the end of the 12-month intervention is given in Table 1. The following data will be collected: (1) Energy and nutrient intakes, (2) Nutrition knowledge; (3) Physical activity levels; (4) Diabetes treatment satisfaction, (5) Anthropometric measurements (weight, height, Body Mass Index), (6) Biochemical assessments: HbA1c and blood lipids (total cholesterol, LDL-C; HDL-C, and triglycerides).

TABLE 1. Data Collection Schedule for Control (usual care) & Intervention Participants\*

| Instrument/clinical parameter                          | Baseline (at recruitment) | Endline (after 12-month intervention) |
|---------------------------------------------------------------|----------------------------------|----------------------------------------------|
| Anthropometric assessments: Height**, body weight             | C, I                             | C, I                                         |
| 24-hour recalls                                               | C, I                             | C, I                                         |
| Diabetes Treatment Satisfaction Questionnaire (DTSQ)          | C, I                             | C, I                                         |
| International Physical Activity Questionnaire (IPAQ)          | C, I                             | C, I                                         |
| Biochemical parameters: HbA1c and blood lipids (LDL, TG, HDL) | C, I                             | C, I                                         |

\* C – Control (usual care); I – Intervention subjects

\*\*Height is measured only at baseline

### **Educational sessions for the intervention participants:**

Research on diabetes self-management interventions has highlighted the important role of ongoing follow-up and support from professionals and members of the social network of the person with diabetes. For example, self-care education with telephone follow-up was associated with improved glycemic control (Piette et al, 2000).

### **Nutrition Education for the Intervention Group Participants:**

**Individual visits:** Since contact time is an important predictor of outcome, participants in the intervention group will attend a total of 7 visits with the dietitian for individual nutrition counseling (20-30 minutes each). Nutrition counseling will be given monthly during the first 3 months and every 2 to 3 months for the remaining intervention period to improve glycemic control, dietary intake, and other outcomes. Participants will be encouraged to follow diets emphasizing fruits, vegetables, and whole grains and to decrease their intake of saturated fat and cholesterol. Dietary advice will be based on the 24-hour food recalls obtained by the dietitian during the visit. During each visit with the dietitian, behavior change goals addressing areas of concern will be identified and participants will be given practical advice in achieving the negotiated goals. Progress towards achieving these goals will be assessed during the following visits. Individualized educational strategies that employ adult education principles and behavior change theories, such as Social Cognitive Theory (Bandura, 1986), including, goal negotiation with the participant will be used to facilitate lifestyle behavior changes.

## Group Education Sessions

### Nutrition Sessions:

Intervention participants will be invited to attend a total of 5 group education sessions on diabetes management (diet & physical activity) conducted in the format of facilitated discussions that include interactive learning exercises. The group education aims to provide knowledge and skills as well as to build the social support network of the participants through regular contact with other people with diabetes and their healthcare team members. Topics for group education are given in Table 2 and include discussions on healthy eating for diabetes management, food portion estimation, food label reading activities, and other topics of relevance to the participants. Physical activity topics will to be covered, including the benefits of physical activity for people with diabetes and practical ways to enhance physical activity in daily life (climbing stairs instead of taking the elevator and performing stretching exercises while watching TV). The pleasure of practicing physical activity will be emphasized. Participants will be encouraged to attend at least three of the five group nutrition education sessions.

Table 2. Group Education Topics for the Intervention Participants

### *Skills for Change Program Group Nutrition Education Sessions*

| Session | Topic                                                            | Discussion Points                                                                                                                                                                                                                                                                                                                                                                                                                                                        |
|---------|------------------------------------------------------------------|--------------------------------------------------------------------------------------------------------------------------------------------------------------------------------------------------------------------------------------------------------------------------------------------------------------------------------------------------------------------------------------------------------------------------------------------------------------------------|
| # 1     | Planning your meals                                              | Interactive discussion on the relationship between healthy eating, metabolic control and health outcomes are highlighted. Concepts on healthy eating for diabetes, basic food groups, serving sizes, and healthful choices are discussed. Dietitian uses food models, pictures and samples of real food. The concept of the plate method for meal planning is introduced. Participants discuss how their typical food group distributions compare with the Plate Method. |
|         | Why being active is beneficial for my health?                    | An interactive discussion will be organized with patients to identify the health benefits of regular practice of physical activity for people with type 2 diabetes                                                                                                                                                                                                                                                                                                       |
| # 2     | Managing your weight                                             | Discussion focuses on food choices, food portions, emotional eating, healthful food choices and tips, and physical activity. Participants are invited to share what benefits they can expect from managing their weights                                                                                                                                                                                                                                                 |
|         | What are the different types of physical activities I should do? | Description of the different types of physical activities and the different context in which physical activity can be practiced. The 3 types of activities included into the current guidelines for physical activity in adults - aerobic physical activity, resistance exercise and strength exercise- will be defined by using examples of activities and demonstration of these activities.                                                                           |

|     |                                      |                                                                                                                                                                                                                                                                                                                                                                                                                                                                                                                                                        |
|-----|--------------------------------------|--------------------------------------------------------------------------------------------------------------------------------------------------------------------------------------------------------------------------------------------------------------------------------------------------------------------------------------------------------------------------------------------------------------------------------------------------------------------------------------------------------------------------------------------------------|
|     |                                      | 
The concepts of frequency and intensity will be defined by using easy to understand explanations and words.
 
Recommendations on safe practice of physical activity (management of glycemia, shoes and feet...) for people with type 2 diabetes will be provided
 
The session will be an interactive discussion involving the patients on the type, frequency and intensity of activities the patient is used to do at this time
                                                                                                     |
| # 3 | Estimating food portions             | 
Dietitian discusses food portion estimation skills and demonstrates using real foods, food models, and household common measures (cups, spoons, etc.). Includes participant exercises involving estimations of different food portions, including UAE traditional food and composite dishes.
 
Participants "guesstimate" before they actually measure and then compare answers.
 
Food models, samples of real foods, household measuring utensils (cups, spoon, etc.) are used.
 
Consistent carbohydrate intake is emphasized
 |
|     | To be active in the daily life       | 
An interactive discussion will be organized with the patients to identify some easy way to be active in the daily life and tips will be provided by the educator.
 
The role of family and friends as support will be emphasized
                                                                                                                                                                                                                                                                                                           |
| # 4 | Choosing healthy fats                | 
Importance of both type of fat and amounts for good health is discussed; Benefits of using herbs & spices instead of fat are emphasized. Participants share recipes and their ideas for modification. Low fat cooking demonstration is conducted (if facilities are available)
                                                                                                                                                                                                                                                              |
| # 5 | Understanding the food labels        | 
Participants learn about the benefits of using food labels and practice how to read food labels or recognize food packages that are lower in fat; participants are invited for a supermarket tour as a follow practical session
                                                                                                                                                                                                                                                                                                                 |
|     | How to keep active in the long-term? | 
Patients will be encouraged to give some suggestions which could help them to maintain their level of physical activity and/or to increase it in the future.
 
Advices on the way of progressively increasing the amount of physical activity in terms of frequency, intensity and duration will be discussed
                                                                                                                                                                                                                              |

### **Physical Activity Sessions:**

The participants will be invited to attend six-week exercise group sessions. The exercise classes, including basic resistance, flexibility, and aerobic exercises will be designed in collaboration with an exercise educator. Sessions will be offered separately for men and women by using indoor and/or outdoor exercise facilities. In addition; participants will be advised to perform exercise sessions at home (3 to 4 sessions per week) exercising at a level of 9 on the Perceived Exertion Scale. The amount of physical activity will be increased progressively through the intervention by encouraging the participants to perform longer and more intense sessions. A video describing sessions, of different durations and at different intensities, providing some explanations and recommendations about the practice of physical activity will be given to each of the participants to help them practice of physical activity at home. This video will be produced in collaboration with UAEU Center for Educational Technology (CET). The physical activity program will be based on the theoretical principles of motivation, self-efficacy, goal-setting, and social support as well as on the simple premise that physical activity can be increased throughout the day at work, at home, and during leisure time. The educational component of physical activity will focus on both physical activity and sedentary behavior as described in the section above. Education will be combined with exercise training sessions. Group exercise sessions will be facilitated by a nurse and exercise specialist. The duration of each session will be 60-90 minutes.

### **Video on Healthy Food Shopping:**

To enhance the practical application of nutrition counseling, a video on healthy food shopping will be produced in collaboration with Ambulatory Healthcare Services and will be displayed in the waiting halls of the three intervention health centers.

### **Facilitating nutrition-related behavior changes:**

The intervention effectiveness will be enhanced by using individualized counseling, provision of sample meal plans and recipes, videos, and peer and professional support (frequent professional contact, group education). Specific concepts on Social Cognitive Theory (SCT) to be incorporated into the intervention to enhance program effectiveness include: (1) Goal setting (negotiate specific behavior change goals on diet and exercise); (2) Role modeling (providing guided practice on diabetes meal planning skills and opportunities for information sharing among participants during group sessions); (3) Enhancing social support peer support, and professional support); (4) Increasing self-efficacy (mastery learning through skill practice e.g. food label reading & food portion estimation skills); (5) Self-monitoring (encouraging participants to keep blood glucose logs); and (6) Enhancing positive outcome expectations (discuss the relationship between food choices, physical activity and metabolic control, relationship between food choices and health).

### **Intervention Monitoring and Evaluation:**

A steering committee consisting of research team members from United Arab Emirates University and the Al Ain Ambulatory Health Services, Abu Dhabi Healthcare Services, will be set up to monitor the intervention implementation and evaluation. During the study, regular meetings will be held by the steering committee to discuss the various aspects of the study, including participant recruitment, intervention staff training needs, and ways of overcoming any potential difficulties faced during the study implementation.

### **Biochemical Methods**

Blood samples will be drawn into dry and EDTA-containing tubes for obtaining serum and plasma respectively. Serum and plasma will be immediately separated after centrifuging the blood sample. Serum and plasma samples will be frozen at -80°C pending analysis. Serum samples will be used to measure the levels of HbA1c, triglycerides, total cholesterol, LDL cholesterol, and HDL cholesterol using a commercial system (UDICHEM ELITE; United Diagnostics Industry as described by Ibrahim et al. (2008).

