## **Study Protocol**

### **Study Title: Skills for Change: Development, Implementation and Evaluation of a Community-based Diabetes Nutrition Education Program for Emirati Adults with Type 2 Diabetes**

#### **Project Summary:**

##### **Project Summary:**

The United Arab Emirates (UAE) with a prevalence of 19.5% of diabetes is considered by the International Diabetes Federation as the country with the second highest prevalence of diabetes in the world. Diabetes is a major risk factor for coronary artery disease, a leading cause of death in the United Arab Emirates. Other complications associated with type 2 diabetes are neuropathy and microvascular damage leading to blindness, and end-stage renal disease. Effective diabetes self-management requires that persons with diabetes acquire the necessary knowledge and skills to change their nutrition-related behaviors for optimal metabolic control. Evidence from randomized controlled studies, observational studies, and meta-analyses support the effectiveness of medical nutrition therapy for diabetes management. Despite the high prevalence of diabetes and its complications in the UAE, very few diabetes education intervention studies have been conducted in representative populations in the country.

We propose a one-year, community-based, cluster randomized study involving 400 Emirati adults with type 2 diabetes that will focus on diet and physical activity to decrease sedentary lifestyle and improve food choices and clinical outcomes, including glycemic control and blood lipids. The primary outcome of the intervention is a change in HbA1c. We expect this project driven by theoretical principles of behavior change and education will enhance the diabetes-related knowledge, skills, and behaviors of the participants. The results of this project will serve as an important guide in the development and implementation of culturally adapted future diabetes management nutrition intervention programs for Emirati adults with type 2 diabetes. The study will be conducted in collaboration with Al Ain Ambulatory Healthcare Services, Abu Dhabi Healthcare Services.

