A recent review highlighted the high prevalence of overweight, obesity, and diet-related non-communicable diseases in the UAE population (Ng et al, 2010). Results from a community-based survey on risk factors for cardiovascular disease conducted among 817 national residents of Al Ain city found that high waist circumference was significantly associated with hypertension and high BMI with diabetes (Baynouna et al, 2009). A previous chronic disease management intervention in the Al Ain Ambulatory Healthcare Services health centers showed improvements in glycemic control, blood lipid profiles, and blood pressure. However, lifestyle-related factors of cardiovascular disease, such as diet and physical activity did not improve possibly due to the limited access to dietitians and other health education specialists to reinforce the physician messages (Baynouna et al, 2010). Saadi and colleagues (2007) found that among people diagnosed with diabetes, only 44% reported seeing a dietitian and 26% of them reported that they did not follow any diet to manage their diabetes.

Evidence from randomized controlled studies, observational studies, and meta-analysis supports the effectiveness of medical nutrition therapy for diabetes (Pastors et al, 2002; Pastors et al, 2003). Diabetes self-management interventions, including those related to weight management, and physical activity have been shown to improve patterns of diabetes management and metabolic control among adults with type 2 diabetes (Norris et al, 2002). Besides, metabolic control achieved through medical nutrition therapy, physical activity, and medications (when needed) improves the quality of life and treats and prevents diabetes complications (ADA, 2007). The UK Prospective Diabetes Study showed that for every percentage decrease in glycosylated hemoglobin (HbA1c), there was a 37% reduction in the risk for microvascular complications and a 21% reduction in the risk for any - **endpoint** or death related to diabetes (Stratton, 2000). Studies on diabetes medical nutrition therapy (MNT) reported reductions in HbA1c, ranging from 0.25% to 2.9%, depending on the type and duration of diabetes. Individual sessions of MNT in these studies ranged from 1 to 5 hours or were a series of 10 to 12 group sessions (2 hours each) (ADA Evidence Analysis Library, 2010).

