## **Methodology**

### **Design and Participants:**

The seven health centers managed by Al Ain Ambulatory Healthcare Services will be the target setting for this study. The primary end-point for this intervention is HbA1c. We aim at a difference in one-year HbA1c value of one-third of the standard deviation which is approximately 1.8 based on recent data from patients with diabetes attending Ambulatory Health Services clinics in the Emirate of Abu Dhabi. Thus, we expect a 0.6 decrease in HbA1c in the

intervention group. We chose to test this difference with a power of 0.8 and a 2-tailed significance level of 0.05. If randomization had been carried out on an individual basis, we would need  $16 \times 9 = 144$  participants per group. However, we have to take into account group randomization. Assuming a design effect of 2, we need approximately 300 per group. However, there will be a gain in efficiency by adjusting for baseline values. Therefore, 200 participants should be adequate per group (i.e. 200 for intervention and 200 for control). Based on this calculation, the seven health centers were randomly assigned as follows: 3 intervention clinics (Al Yahar, Al Muweiji, & Hilli) and 4 control clinics (Al Maqam, Al Zakher, Niyadat, & Mezyad). The health center setting (urban vs. suburban) and size (large vs. small) were considered during the randomization. The assignment of the health centers to the intervention versus control groups was stratified by the center sizes and center locations. Of the 7 health centers, 3 are large urban centers, two are small urban centers, and two are large suburban centers. One large urban, one large suburban and two small urban centers were randomly assigned to the control group, and the remaining 3 centers were assigned to the intervention group.

Exclusion criteria are: Very advanced age (>70 Y), patients with severe complications, such as renal or heart failure, blindness, or other morbidities that can prevent active participation in the program. Moreover, patients with contraindications to the required physical activity may be excluded from the structured physical activity program upon the recommendation of their attending physicians. Verbal and written informed consent will be obtained from all the participants. Ethics approval for the project will be obtained from the relevant research ethics committees (UAE University Research Affairs and Al Ain Medical District Human Research Ethics Committee).

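### The protocol assigns HbA1c, the primary endpoint, to serum, a specimen from which the red cells have been removed, so followed as written it yields no valid primary result

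*Protocol*

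**What the plan says.** HbA1c is the primary endpoint throughout. The Project Summary says "The primary outcome of the intervention is a change in HbA1c", and Design and Participants says "The primary end-point for this intervention is HbA1c". Table 1 schedules it at baseline and after 12 months in both arms.

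The laboratory procedure appears only under Biochemical Methods, in four steps:

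- Collection: "Blood samples will be drawn into dry and EDTA-containing tubes for obtaining serum and plasma respectively".
- Processing: "Serum and plasma will be immediately separated after centrifuging the blood sample".
- Storage: "Serum and plasma samples will be frozen at -80°C pending analysis".
- Assay: "Serum samples will be used to measure the levels of HbA1c", in one list with the four lipid measures, run on a named commercial system with a reference to a 2008 publication for the method.

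No whole-blood, packed-cell or haemolysate aliquot is described anywhere. Nor is a point-of-care test, a separate HbA1c method, or the use of HbA1c values from clinic records.

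**The concern.** The named specimen does not contain the analyte. HbA1c is the glycated fraction of haemoglobin, and haemoglobin is carried in red cells. Serum is what remains after clotting and removal of the cells. Any haemoglobin found in it would come from cells that broke during handling, so a result would reflect haemolysis and not glycaemic control.

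The primary comparison, the sample-size argument and the glycaemic part of the second objective all depend on HbA1c. An error in the specimen for this one analyte puts the main result of the trial at risk. It also cannot be repaired afterwards: if only serum and plasma are in the freezer, a baseline HbA1c cannot be recovered once the baseline visit has passed.

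**Working it through.** The point turns on the specimen chain and not on a calculation, so the first step is to set the statements side by side.

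| Step | What the protocol specifies | Red cells available for assay? |
|---|---|---|
| Collection | Dry tube for serum, EDTA tube for plasma | Yes, in both tubes before spinning |
| Processing | Centrifuge, separate serum and plasma at once | Removed from both fractions |
| Storage at -80°C | Serum and plasma | None described as kept |
| Assay of HbA1c | Serum | No |

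The background section supplies the definition of the analyte when it speaks of "every percentage decrease in glycosylated hemoglobin (HbA1c". The conflict is thus internal to the protocol: it calls the analyte a form of haemoglobin, then assigns it to a fraction from which the haemoglobin-bearing cells have been taken away. The plasma does not help either, since it too is cell-free.

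**Extent.** Planned participants: 200 per group × 2 groups = 400. Scheduled HbA1c assessments per participant: 2. Planned determinations: 400 × 2 = 800. This is the maximum, because the protocol itself anticipates retention problems.

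**The sample-size figures.** These were checked to see whether the specimen error alters them.

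- Inputs from Design and Participants: SD about 1.8, difference 0.6, power 0.8, two-sided 0.05.
- The protocol's rule: 16 × (1.8/0.6)² = 16 × 9 = 144 per group.
- Normal approximation: 2 × (1.960 + 0.842)² × 9 ≈ 141.3, rounded up to 142 per group. The stated figure reproduces.
- Design effect of 2: 2 × 144 = 288, which the protocol rounds up to approximately 300.

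The specimen problem changes none of these numbers. It does bear on the last step, where the protocol goes from about 300 to 200 per group on the strength of adjusting for baseline values.

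**If only the baseline values were lost.** Suppose the error were found after baseline and the 12-month samples were handled properly. With no baseline covariate, and on the protocol's own design effect of 2, 200 per group is worth 200/2 = 100 independent participants per group. The standard error is 1.8 × √(2/100) = 0.2546, and 0.6/0.2546 = 2.357. Power is Φ(2.357 − 1.960) = Φ(0.397) ≈ 0.65, against the intended 0.80. If both time points were affected, there would be no primary analysis at all.

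**The case against.** The strongest counter-argument is that this is a drafting slip. An EDTA tube is drawn and plasma is prepared, yet no analyte is assigned to that plasma, while HbA1c sits in one sentence with four lipid measures. HbA1c may simply have been folded into the serum panel in error. The SD of 1.8 comes from recent data on patients with diabetes in the same health service, which suggests that HbA1c is already measured there in a workable way. A competent laboratory might well notice the problem. The text also does not say that the cells are discarded, and some detail may lie in the 2008 publication it points to.

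Part of this stands. Actual invalidity is conditional on the laboratory following the text, and the accurate statement is that no whole-blood specimen is described, not that one is known to be absent. The figure of 800 counts planned measurements; it does not predict how many will fail.

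The rest does not rescue the wording. The EDTA tube is expressly assigned to plasma, so it cannot be read as an implied whole-blood sample. The 2008 publication does not appear in the reference list as shown, and a whole-blood step there would contradict the stated serum specimen. The reference to health-centre standard protocols under Safety Considerations concerns the risks of drawing blood and not specimen handling. This is also not detail left to a statistical analysis plan: the protocol states a specimen, and it is the wrong one.

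**Conclusion.** The concern holds and must be fixed. As written, the protocol directs the primary endpoint to a specimen that cannot yield it, for every participant, in both arms and at both time points: up to 800 planned determinations. Certainty is high that the instruction is wrong. Whether the primary result would in fact be lost depends on whether the laboratory follows the instruction literally, which the protocol does not settle. The conclusion rests on the protocol's own definition of HbA1c as glycosylated haemoglobin, on haemoglobin being a red-cell constituent, and on Biochemical Methods being the only description of the assay. The sample-size figures themselves are unaffected.

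**What to change.** Amend Biochemical Methods to separate HbA1c from the serum lipid panel. State that HbA1c is assayed on an aliquot of EDTA whole blood taken before centrifugation, and give its storage conditions and assay method. Confirm that the named commercial system accepts that specimen, or name the method that will be used. Keep serum for triglycerides and for total, LDL and HDL cholesterol. Bring any laboratory manual into line.

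The cost is small: a change of wording and one aliquot step. The EDTA tube is already collected, so no extra blood is drawn.

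If any samples have already been processed, establish from laboratory records which specimen was used for HbA1c and document the answer before the primary analysis. If it was whole blood, correcting the text is sufficient. If it was serum, those values should not be used as the primary endpoint, and the loss of baseline adjustment should be reflected in a revised power statement.
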